## 10. ADVERSE EVENTS

### 10.1 Definitions

Adverse Event (AE). According to International Conference on Harmonization (ICH) E2A, an adverse event (or adverse experience) is any untoward medical occurrence in a subject or clinical investigation subject administered a pharmaceutical product and which does not necessarily have to have a causal relationship with this treatment. An AE can therefore be any unfavourable and unintended sign (including an abnormal laboratory finding, for example), symptom, or disease temporally associated with the use of a medicinal product, whether or not considered related to the medicinal product.

Serious Adverse Event (SAE). A serious adverse event (SAE) is any untoward medical occurrence that, at any dose:

- Results in death
- Is life-threatening, (Note: The term "life-threatening" in the definition of "serious" refers to an event in which the subject was at risk of death at the time of the event. It does not refer to an event, which hypothetically might have caused death if more severe.)
- Requires hospitalization or prolongation of existing hospitalization
- Results in disability/incapacity or
- Is a congenital anomaly/birth defect.

Medical or scientific judgment should be exercised in deciding whether reporting is appropriate in other situations, such as important medical events that may not be immediately life threatening or result in death or hospitalization but may jeopardize the subject or may require medical or surgical intervention to prevent one of other outcomes listed in the above definition. These should also be considered serious.

Examples of such events are invasive or malignant cancers, intensive treatment in emergency room or at home for allergic bronchospasm, blood dyscrasias or convulsions that do not result in hospitalization, or development of drug dependency or drug abuse.

For the purpose of this trial, the information related to the emergency visits due to hyperammonemia will be collected specifically on the CRF, and should not be consider an AE or SAE.

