## 10.2 Adverse event with interventional medication

### Favipiravir Adverse Drug Reactions

- Major adverse drug reactions include increase of uric acid serum level (~4.8%), diarrhea (~4.8%), decrease neutrophil count (1.8%), and increase in AST and ALT (1.8%, 1.6%) respectively.
- Other clinically significant ADRs include skin rash, neurological and psychiatric symptoms (e.g. suddenly running away, wandering around), anaphylactic shock, pneumonia, hepatic dysfunction, acute renal failure, decrease in white blood cell count and platelet count, and hemorrhagic colitis.

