### HYDROXYCHLOROQUINE ADVERSE DRUG REACTIONS

- Adverse drug reactions have been reported after administering hydroxychloroquine include:

- Blood disorders: Bone marrow suppression (anemia, leukopenia, agranulocytosis, and thrombocytopenia)
- Cardiac disorders: QTc prolongation
- Ear disorders: Vertigo, tinnitus, and nystagmus
- Eye disorders: Irreversible retinopathy with retinal pigmentation changes and visual disturbances
- Gastrointestinal disorders: Nausea, vomiting, diarrhea, and abdominal pain
- Hepatobiliary disorders: Liver function tests abnormal and acute hepatic failure
- Metabolism and nutrition disorders: Decreased appetite, hypoglycemia, porphyria, weight decreased
- Nervous system disorders: Headache, dizziness, seizure, ataxia and extrapyramidal disorders such as dystonia
- Psychiatric disorders: Affect/emotional lability, nervousness, irritability, nightmares, psychosis, and suicidal behavior
- Skin and subcutaneous tissue disorders: Rash, pruritus, pigmentation disorders in skin and mucous membranes, hair color changes, alopecia.

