#### 10.4 Handling of Serious Adverse Events

All adverse drug events encountered during the clinical study will be reported on the CRF. Serious adverse events (SAEs), whether or not associated with study medication administration, will be recorded both on the Adverse Event form of the CRF as for non-serious AE and the SAE form.

ALL SAEs occurring during this study and up to 30 days after a subject discontinued or completed the study, whether or not related to the administration of study medication, must be reported by faxing the completed SAE form, after reviewing the report for consistency and accuracy within 24 hours of awareness by the investigator, to KAIMRC / IRB.

As far as possible, investigators should follow-up participants with AEs until the event is resolved or until, in the opinion of the investigator, the event is stabilized or determined to be chronic. Details of AE resolution must be documented in the CRF. Participants should be followed-up for 30 days after receiving the last dose of study medication and any AEs, which occur during this time, should be reported according to the procedures outlined above. Any significant changes in AEs should be reported even though the subject has completed the study, including the protocol-required post-treatment follow-up.

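### Section 10.1 exempts emergency visits for hyperammonemia from AE and SAE status, against its own general definitions and with no reason given for this trial

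*Protocol*

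**What the plan says.** Protocol Section 10.1 defines an adverse event broadly, as "any untoward medical occurrence in a subject or clinical investigation subject administered a pharmaceutical product", whatever the cause. It adds that an AE may be "any unfavourable and unintended sign (including an abnormal laboratory finding, for example), symptom, or disease temporally associated with the use of a medicinal product". Seriousness depends on outcome, and one criterion reads "Requires hospitalization or prolongation of existing hospitalization".

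The section then closes with a rule specific to this trial: information on "emergency visits due to hyperammonemia will be collected specifically on the CRF, and should not be consider an AE or SAE".

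Section 10.2 lists "hepatic dysfunction, acute renal failure" among the clinically significant reactions to favipiravir, and "Liver function tests abnormal and acute hepatic failure" for hydroxychloroquine. Section 10.3 has every AE recorded regardless of its relation to study medication. Section 10.4 covers "ALL SAEs occurring during this study and up to 30 days after a subject discontinued or completed the study", again regardless of relation, with a report within 24 hours of the investigator's awareness.

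**The concern.** The closing sentence of 10.1 is an instruction to sites about what to report. It is not background, and it is not analysis detail that could be left to a statistical analysis plan. Taking an event out of AE and SAE status needs a reason, for example that it is an endpoint or an expected part of the disease under study. The protocol gives none for hyperammonemia.

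Raised ammonia can be a sign of hepatic failure, and both study drugs carry a listed hepatic reaction. What is at stake is an event that sites are told not to classify as an AE or SAE. It could go without an expedited report and without being counted in the safety comparison of Section 9.4.

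**Working it through.** The point is textual and the protocol states no figure to reproduce. The check sets the sections side by side.

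1. **Rule against definition, both in 10.1.** A visit to an emergency department with raised ammonia is untoward, and the raised ammonia is an abnormal laboratory finding. Under the general definition it is an AE. If it leads to admission, it meets the hospitalization criterion and is an SAE. The closing sentence says it is neither, and makes no exception for a visit that ends in admission or death. The text just before it also points the other way: its examples of events to be treated as serious without hospitalization include intensive emergency-room treatment of allergic bronchospasm.

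2. **Rule against the reporting sections.** Section 2.5 (all AEs and SAEs monitored and recorded), Section 10.3 (all AEs) and Section 10.4 (all SAEs, 24 hours, 30-day tail) contain no exception and do not refer to this one.

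3. **Search for a rationale.** Hyperammonemia is absent from the background, objectives, endpoints, eligibility criteria, flow chart, listed drug reactions and AE grading appendix. The laboratory panel in the flow chart is CBC, renal profile and LFT. Ammonia is not named.

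4. **Where the rule could act.** Participants are inpatients, so an emergency visit would mostly be a return after discharge. Section 7.4 ends follow-up at discharge or day 28, but the SAE window in 10.4 runs 30 days beyond completion or discontinuation. Such a visit can therefore fall inside the reporting period.

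5. **What would be lost.** An exempted visit would skip the 24-hour SAE report. It would not count in the proportions with an SAE or a Grade 3 or higher AE, which Section 9.4 compares by Fisher's exact test.

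6. **Size.** The protocol gives no rate. As an assumption only, take 0 to 2 such patients among 520. If both were in one arm of 260, and neither had another qualifying event, that arm's proportion would change by at most 2/260 = 0.77 percentage points. Overall the change would be at most 2/520 = 0.38 percentage points.

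**The case against.** The strongest reply is that the sentence exempts a type of visit, not a disease. Acute hepatic failure, abnormal liver tests, hospitalization and death keep their status under 10.1. A reader might infer that a patient returning with encephalopathy after drug-induced liver injury would certainly drop out of SAE reporting. The text does not support that. It would happen only if the site labelled the whole episode a hyperammonemia visit and did not report the underlying diagnosis.

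A reader might also infer that the Data and Safety Monitoring Board would not see these events. That is not shown. The visits go on the CRF, and Section 12.2 gives the board the unblinded trial data, not only SAE forms.

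The conflict with 10.4 is also not a strict contradiction. Section 10.4 asks for all SAEs, and an exception within the definition narrows what counts as one. The direct contradiction is inside 10.1; 10.3 and 10.4 fail to reflect the exception. These three points stand.

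Other facts reduce the exposure. Severe liver damage is excluded at entry, and liver tests are frequent during treatment. The rule applies equally to both arms, and controls may receive hydroxychloroquine under Section 6 (Reference Therapy), so no between-arm bias is shown. None of this supplies a reason for the exemption.

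**Conclusion.** The rule is wrong as written. It contradicts the general AE and SAE definitions in the section that contains it, and nothing in the protocol justifies it for this population. The realistic consequence is a missed expedited report, or a missed count, for a rare post-discharge visit labelled as hyperammonemia. The effect on the Fisher comparison would be negligible, and efficacy, sample size and randomization are untouched. This is a minor reconciliation.

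The size rests on the assumed 0 to 2 patients, which has no source in the protocol, and on sites applying the sentence literally. A reader might take the sentence as text left over from another protocol. The appendix grades skin necrosis at an injection site although both study drugs are given by mouth or nasogastric tube, which fits that reading. It remains an inference, and the contradiction does not depend on it.

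**What to change.** Delete the closing sentence of Section 10.1, so that emergency visits with hyperammonemia are classified under the general AE and SAE definitions like any other event. If there is a reason to keep it, state that reason for this population and reconcile the exemption explicitly with 10.1, 10.3 and 10.4. The CRF item need not be removed, because collecting the visit does no harm once the classification is normal. Any visit already recorded under the rule should be checked against the general definitions.

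Under Section 13.2 the cost is a written amendment approved by the sponsor and the investigators. As a minor amendment, it must be notified to the Ethics Committee.

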## 10.2 Adverse event with interventional medication

### Favipiravir Adverse Drug Reactions

- Major adverse drug reactions include increase of uric acid serum level (~4.8%), diarrhea (~4.8%), decrease neutrophil count (1.8%), and increase in AST and ALT (1.8%, 1.6%) respectively.
- Other clinically significant ADRs include skin rash, neurological and psychiatric symptoms (e.g. suddenly running away, wandering around), anaphylactic shock, pneumonia, hepatic dysfunction, acute renal failure, decrease in white blood cell count and platelet count, and hemorrhagic colitis.

### HYDROXYCHLOROQUINE ADVERSE DRUG REACTIONS

- Adverse drug reactions have been reported after administering hydroxychloroquine include:

- Blood disorders: Bone marrow suppression (anemia, leukopenia, agranulocytosis, and thrombocytopenia)
- Cardiac disorders: QTc prolongation
- Ear disorders: Vertigo, tinnitus, and nystagmus
- Eye disorders: Irreversible retinopathy with retinal pigmentation changes and visual disturbances
- Gastrointestinal disorders: Nausea, vomiting, diarrhea, and abdominal pain
- Hepatobiliary disorders: Liver function tests abnormal and acute hepatic failure
- Metabolism and nutrition disorders: Decreased appetite, hypoglycemia, porphyria, weight decreased
- Nervous system disorders: Headache, dizziness, seizure, ataxia and extrapyramidal disorders such as dystonia
- Psychiatric disorders: Affect/emotional lability, nervousness, irritability, nightmares, psychosis, and suicidal behavior
- Skin and subcutaneous tissue disorders: Rash, pruritus, pigmentation disorders in skin and mucous membranes, hair color changes, alopecia.

### 10.3 Handling of Non-Serious Adverse Events

All AEs encountered during the clinical study will be reported on the CRF. Adverse events, whether or not associated with study medication administration, will be recorded on the Adverse Event form of the CRF.

The information to be entered in the CRF will include:

- The time of onset of any AE or the worsening of a previously observed AE
- The specific type of reaction in standard medical terminology
- The duration of the AE (start and stop dates)
- The severity of the adverse event (AE). The severity should be rated as:

- Mild: discomfort noted, but no disruption of normal daily activity.
- Moderate: discomfort noted of sufficient severity to reduce or adversely affect normal activity.
- Severe: incapacitating, with inability to work or perform normal daily activity.
- An assessment of the relationship of the adverse event (AE) to the study medication, i.e., according to the definitions below:
  - Related: with a reasonable causal relationship to the investigational product
  - Not Related: without a reasonable causal relationship to the investigational product
  - Other: in such case, investigator's causality assessment should be clearly specified.
- Description of action taken in treating the AE and/or change in study medication administration or dose.

As far as possible, all investigators should follow-up participants with AEs until the event is resolved or until, in the opinion of the investigator, the event is stabilized or determined to be chronic. Details of AE resolution must be documented in the CRF. Any significant changes in AEs should be reported even though the subject has completed the study, including the protocol-required post-treatment follow-up.

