### For secondary endpoints:

- Quantitative variables such as duration of ICU stay and change from baseline in clinical scores, etc., are expected to have reasonably skewed distributions and may be subject to censoring (e.g., for subjects in hospital on Day 28; these will be compared between randomized arms using non-parametric tests (e.g., Wilcoxon's Test adapted, if necessary, to handle censoring).
- Analysis of the ordinal scale endpoints will use a proportional odds model with an indicator variable for randomized treatment. The Wald test will be used to generate a p-value comparing treatments, as well as the estimated proportional odds ratio comparing treatments with associated 95% CI.

- Analysis of AE data will primarily be descriptive based on MedDRA coding of events. The proportion of subjects experiencing an SAE and the proportion experiencing a Grade 3 or higher AE will be compared between randomized arms using Fisher's Exact Test.

For enrolled subjects who were not randomized (i.e. screen failures) or who were randomized but did not receive the treatment, the final analysis will detail safety (deaths and SAEs), and reasons they were not randomized or did not received treatment respectively.

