## APPENDIX

1. Classification of Adverse Events using the NIH Common Terminology Criteria for Adverse Events (CTCAE), Version 4.0.

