| Definition                                        | A disorder characterized by excitement of psychotic proportions manifested by mental and physical hyperactivity, disorganization of behavior and elevation of mood.         |                                                                                   |                                                                                                                 |                                                                                               |       |
| Electrocardiogram QT corrected interval prolonged | Average QTc 450 - 480 ms                                                                                                                                                    | Average QTc 481 - 500 ms                                                          | Average QTc $\geq$ 501 ms; $>60$ ms change from baseline                                                        | Torsade de pointes; polymorphic ventricular tachycardia; signs/symptoms of serious arrhythmia |       |
| Definition                                        | A finding of a cardiac dysrhythmia characterized by an abnormally long corrected QT interval.                                                                               |                                                                                   |                                                                                                                 |                                                                                               |       |
| Skin and                                          | Asymptomatic or                                                                                                                                                             | Moderate;                                                                         | Severe or medically                                                                                             | Life-threatening                                                                              | Death |

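### Section 10.3 rates adverse events on a three-level scale that does not give the Grade 3 or higher variable tested in section 9.4, and the protocol does not reconcile the two

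*Protocol*

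**What the plan says.** Section 10.3 lists what goes on the adverse event form under the lead-in "The information to be entered in the CRF will include". One item is severity: "The severity of the adverse event (AE). The severity should be rated as", followed by three levels. Mild and moderate are defined by discomfort and its effect on normal activity. The third is "Severe: incapacitating, with inability to work or perform normal daily activity". Section 10.4 extends this to serious events, which "will be recorded both on the Adverse Event form of the CRF as for non-serious AE and the SAE form".

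Section 9.4, under the secondary endpoints, says that adverse event data will mainly be described, with two inferential comparisons by Fisher's exact test. One is the proportion with a serious adverse event. For the other, "the proportion experiencing a Grade 3 or higher AE will be compared between randomized arms". The grading scale is not named there.

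The only graded scale in the protocol is in the Appendix, titled "Classification of Adverse Events using the NIH Common Terminology Criteria for Adverse Events (CTCAE), Version 4.0". The table printed after the reference list gives criteria for Grades 1 to 5. Its row "Electrocardiogram QT corrected interval prolonged" sets Grade 3 by an average QTc of 501 ms or more, together with an entry for a change of more than 60 ms from baseline. Neither 9.4 nor 10.3 refers to this appendix.

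**The concern.** Sites are told to record severity on one scale, and the analysis tests a threshold on another. No rule links severe to Grade 3 or higher. The Grade 3+ comparison is the protocol's only inferential comparison of adverse event severity. As written, its result depends on which scale the analyst takes, or on a mapping that nobody has stated.

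The events most exposed are those found by measurement and not by complaint: QTc prolongation, and liver or blood count changes. These are among the reactions that sections 1.5.5.1 and 10.2 list for the two drugs. A scale built on discomfort and activity is a poor instrument for them.

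**Working it through.** The protocol states no figure to reproduce, so the check sets the sections side by side.

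1. **Levels.** Section 10.3 has three levels and the CTCAE appendix has five. The criteria differ, and no correspondence is stated.

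2. **A value-based event.** Take a patient with an average QTc of 501 ms or more, a rise of more than 60 ms from baseline, and no symptoms.
   - Appendix: Grade 3, on the ECG alone.
   - Section 10.3: severe requires incapacity, so the event is not severe. Even mild requires discomfort, so strictly the event fits none of the three levels.
   - Result: the event counts in the Grade 3+ test if CTCAE is applied, and not if the 10.3 rating is used as the grade. The same reasoning holds for a symptom-free laboratory change, which section 10.1 counts as an adverse event.

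3. **A symptom-based event.** In the headache row of the appendix, Grade 2 limits instrumental activities and Grade 3 limits self-care. A patient who cannot carry out normal daily activity but manages self-care could be severe under 10.3 and Grade 2 under CTCAE. The mismatch can therefore also raise the count.

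4. **Can the grade be recovered later?** For QTc, yes, from the ECG values. For many other rows, Grade 3 is a bedside judgment: limits on self-care (dyspnea, headache, abdominal pain) or an indication for hospitalization (diarrhea, nausea, vomiting). The fields listed in 10.3 do not record these judgments, and a three-level rating does not contain them.

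5. **Coverage of the printed table.** Section 10.2 names raised uric acid, raised AST and ALT, and a fall in neutrophils among the major favipiravir reactions. The printed table has no rows for these, so the full CTCAE v4.0 is needed.

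6. **Does grading from measured values give a fair comparison?** The flow chart in section 8 differs by arm. The counts below are of days after D0, reading the unlabelled columns as every day in between (an assumption).
   - Laboratory, study drug: D1 to D10, D14 and D21, so 10 + 2 = 12 days. Standard of care: D1, D5, D10 and D21, so 4 days. Ratio 12/4 = 3.
   - ECG, study drug: D1 to D5 and D10, so 5 + 1 = 6 days by the flow chart, or 10 days by section 7.3 (daily on days 1 to 10). Standard of care: D1, D5 and D10, so 3 days. Ratio 6/3 = 2, or 10/3 = 3.3.
   - With equal true rates, looking two to three times as often would find more threshold crossings on study drug. Grades taken from all values would therefore bias the test against the combination. The days scheduled in both arms are the standard-of-care days.

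**The case against.** A reader might infer more than the protocol supports.

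- **That the Grade 3+ test cannot be computed.** It can if CTCAE is applied. The appendix is titled as the classification of adverse events, the word grade fits only that scale, and the QTc row works from recorded values. What cannot be done is to compute the test from the 10.3 rating without an unstated mapping.
- **That the CRF holds only the three-level rating.** The list in 10.3 is introduced as what the form will include, and the CRF is not among the documents. A grade field may exist. Still, 10.3 gives one severity rule, and it is not a grade.
- **That symptom-free QT events are missed by the trial.** They are not. ECGs are scheduled in both arms (section 8), with daily monitoring on study drug (section 7.3), and QT prolongation is secondary endpoint 8 in section 2.4. They drop out of one test only, and only if the 10.3 rating is used as the grade, which no section instructs.
- **That life-threatening and fatal events are lost for want of a level 4 or 5.** They are serious by definition (section 10.1), go on the serious event form (10.4) and enter the separate serious event test (9.4). Missing upper levels do not by themselves change a count of Grade 3 or higher.

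The strongest argument that remains is that the scale could be named in the statistical analysis plan, which 9.4 promises. That would settle the definition. It would not supply bedside grades that sites were told to rate on another scale. In an open-label trial, whoever assigns grades later may also know the arm. The instruction to sites has to be corrected in the protocol.

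**Conclusion.** The concern holds as an inconsistency that should be corrected: two severity scales, no link between them, and a rating instruction that does not yield the variable that 9.4 tests. Measurement-based events are the most exposed. They would leave the Grade 3+ count if the 10.3 rating served as the grade, while remaining visible through the ECGs, the laboratory data and the separate QT endpoint.

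The size cannot be quantified. The protocol gives no expected Grade 3+ rate and no share of symptom-free events, so any figure would be assumed. The conclusion rests on the wording of 9.4, 10.3, 10.4 and the appendix, and on no grade field being described in the protocol. If the CRF already records a CTCAE grade, the remaining need is to align the wording.

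**What to change.** - **Section 10.3:** replace the three-level rating with the CTCAE v4.0 grade, 1 to 5. Refer to the full CTCAE, because the printed extract lacks uric acid, AST/ALT and neutrophil rows. Record the grade in the eCRF. Since 10.4 uses the same form, serious events are then covered too.
- **Section 9.4:** state that Grade 3 or higher means this recorded CTCAE v4.0 grade.
- **Between-arm test:** take laboratory and QTc grades from measured values only on post-randomisation days scheduled in both arms: laboratory D1, D5, D10 and D21; ECG D1, D5 and D10. Report the other study-drug-arm values descriptively.

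The cost is one eCRF field and a few sentences, with sites grading on five levels instead of three. The between-arm test also gives up the values from study-drug-only days. On the reading of the flow chart used above, that is 12 - 4 = 8 laboratory days, and 6 - 3 = 3 ECG days (10 - 3 = 7 if ECGs follow section 7.3). Events seen only on those days appear in the descriptive tables and not in the test.
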